### Recruitment

Patients referred from primary care to ENT specialist services and attending either a conventional face-to-face consultant-led clinic or a remote clinic will be recruited into the study. We will send an invitation letter explaining the purpose of the study to the patients, along with their clinic invitation letter, and potential participants will be approached prior to their initial clinic appointment.

On their attendance at clinic, patients will be approached by a member of the healthcare team and will be given the study information package and offered the opportunity to ask questions and discuss their potential participation in the study. For those patients who agree to take part, this will be documented in their medical records and the research team will begin informed consent procedures.

Patients will not be randomised, and the study will not have any influence on the allocation of patients to the traditional or the remote pathway, which will be arranged by UHB, on a weekly basis, according to clinical priority and waiting length per referral. The clinic allocation process is regulated by the hospital and patients are allocated in consecutive order to either a face-to-face or a remote clinic, until all the slots of that week have been filled, before booking patients for a different week. Patient prioritisation is made in the form of urgency, without reference to the method of clinic delivery. Patient demographics, disease severity or other characteristics are not used in regards to allocation to an in-person or remote clinic appointment.

This will ensure that selection bias will not be introduced on the patients seen in the remote pathway, compared with the cohort seen face-to-face. We will assess propensity scores for the patients and assess their propensity score weighting using logistic regression.

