### Quantitative analysis

Quantitative analysis will examine patient characteristics, symptom resolution, discharge rates, consultant review volumes and waiting times, as well as environmental sustainability (assessed by the carbon footprint of clinics and patient travel).

Acceptability will be gauged using a 5-point Likert scale and open-ended questionnaires. Descriptive statistics (means, SD and CIs) will summarise continuous data, while discrete variables will be reported as counts and percentages. Standard regression models (95% CIs) and subgroup analyses will compare groups, with outcomes reported in scoring scales analysed as continuous variables. Count models will be used to count outcomes (such as number of appointments) and time-to-event models to assess time to definitive treatment/decision. A 5-point Likert scale questionnaire will further capture how different clinic permutations align with patient expectations. Missing data will be handled initially by descriptive means, aiming to describe the proportion of missing data, its characteristics and potential mechanisms and then using multiple imputation methodology. Analyses will adjust for age, sex, IMD quintile, baseline symptoms, presenting condition category, comorbidity count and distance to clinic; robustness will be checked using propensity score weighting. Differential follow-up will be handled with time-to-event methodology, using Cox proportional hazards, accounting for the differences in the follow-up duration across groups with different pathology.

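### The claim that hospital slot allocation excludes selection bias is not supported: the rule dividing patients between pathways is not stated, and the listed covariates omit referral priority, waiting length and booking week

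*Protocol article*

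**What the plan says.** All but one of these statements are in the Recruitment section of the protocol article.

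- Allocation is outside the study's control: "Patients will not be randomised, and the study will not have any influence on the allocation of patients". The hospital arranges it "on a weekly basis, according to clinical priority and waiting length per referral".
- Within a week, "patients are allocated in consecutive order to either a face-to-face or a remote clinic, until all the slots of that week have been filled".
- Two sentences then separate urgency and severity from the choice of mode: "Patient prioritisation is made in the form of urgency, without reference to the method of clinic delivery", and "Patient demographics, disease severity or other characteristics are not used in regards to allocation to an in-person or remote clinic appointment".
- The conclusion drawn is: "This will ensure that selection bias will not be introduced on the patients seen in the remote pathway".
- On propensity scores: "We will assess propensity scores for the patients and assess their propensity score weighting using logistic regression". No covariates are named.

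The Quantitative analysis section fixes the adjustment set: "Analyses will adjust for age, sex, IMD quintile, baseline symptoms, presenting condition category, comorbidity count and distance to clinic". Propensity score weighting is given there as the robustness check. The strengths and limitations box mentions selection bias only for people who do not attend this Trust, not between the two pathways.

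**The concern.** A booking process that nobody randomised cannot guarantee comparable groups. The article names what drives that process (priority, waiting length, the weekly booking cycle), and none of these is among the seven covariates. Baseline symptoms and presenting condition category are partial proxies for priority at best.

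If patients are taken in order from a list sorted by urgency and wait, and one mode's slots tend to fill before the other's, position on the list influences the mode even though nobody chooses it on clinical grounds. Urgent or long-waiting patients may differ in how many appointments they need and how soon they are treated. A difference between pathways could then partly reflect who was booked where.

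The comparisons at stake are number of appointments, waiting time and time to definitive treatment, costs, and CO2eq. The proportion successfully managed remotely and the re-presentation rate are defined in the Primary outcome section for remote patients only, so confounding between pathways does not bias them as such.

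**Working it through.** The point rests on no figure stated in the plan, so there is none to reproduce. The first check sets the text side by side. The second is an illustration whose inputs are mostly assumed.

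**1. Allocation drivers against the adjustment list**

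| Named in Recruitment as a basis of allocation | In the Quantitative analysis covariate list? |
|---|---|
| Clinical priority | No (baseline symptoms and condition category are partial proxies) |
| Waiting length | No |
| Week of booking | No |

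For the propensity model no comparison is possible, because its covariates are not listed.

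**2. What the unstated filling rule could do**

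Input from the article: about 80 patients per cohort per week (Recruitment), taken as 80 + 80 = 160 slots. Assumed: 30% of referrals urgent; the list sorted by urgency and then longest wait; waits drawn from a skewed distribution with mean 40 arbitrary units. Averages over 400 simulated weeks:

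| Filling rule | Urgent, face-to-face v remote | Mean wait, face-to-face v remote |
|---|---|---|
| Strict alternation | 30.2% v 29.6% | 40.1 v 39.4 |
| Remote share rising from 30% to 70% down the list | 38.0% v 21.7% | 42.4 v 37.5 |
| Face-to-face filled completely first | 60.2% v 0% | 49.8 v 30.1 |

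The last row agrees with direct arithmetic: 0.30 × 160 = 48 urgent patients, all within the first 80 slots, and 48/80 = 60%.

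**3. From imbalance to bias**

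For a binary outcome compared between pathways, before adjustment:

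bias = (difference in urgent share) × (outcome difference, urgent v routine).

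For scale, with 150 per group and p = 0.83 in both:

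SE = √(2 × 0.83 × 0.17 / 150) = 0.0434, so the 95% half-width is 1.96 × 0.0434 = 0.085, or 8.5 points.

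The 83% is the remote-only pilot result from the Introduction. It is used here only to set a plausible variance. The article defines no between-pathway comparison of that proportion.

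| Imbalance (assumed) | Outcome difference (assumed) | Bias | Two-sided type I error at nominal 5% |
|---|---|---|---|
| 0 | any | 0 | 5% |
| 10 points | 10 points | 1 point | 5.6% |
| 20 points | 20 points | 4 points | 15% |
| 30 points | 30 points | 9 points | 55% |

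Applied to the rules in step 2 with a 10-point outcome difference, alternation gives 0.006 × 10 = 0.06 points, the gradient 0.163 × 10 = 1.6 points, and filling one mode first 0.602 × 10 = 6.0 points. The last is a boundary case, not an expectation.

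**The case against.** The strongest reply is that the Recruitment section, read as a whole, already separates priority from mode. Urgency is set without regard to how the clinic is delivered, and severity and other characteristics are said not to enter the choice of mode. On that reading, priority and wait decide only the week in which a patient is seen, and mode follows from consecutive filling within the week. Any filling order unrelated to list position, not just strict alternation, then leaves no systematic imbalance within a week. This stands, and it is why bias cannot be called present. It does not rescue the guarantee: the filling order is not stated, and if the mix of remote and face-to-face slots varies between weeks, week of booking still links priority to mode.

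The bias figures are also unadjusted and rest on assumed inputs. Adjustment for baseline symptoms and condition category would remove part of any effect, and excluding suspected cancer removes one urgent group. That stands too.

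A reader might infer four stronger things that the article does not support:

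- **That the propensity check repeats the omission.** Its covariates are not listed, and a condensed article may leave them to a fuller document.
- **That the primary success proportion is confounded.** It is defined for remote patients only.
- **That each group closes separately at 150, so the groups come from different weeks.** The text reads at least as naturally as joint sampling until both reach 150.
- **That patients rebooked from remote to face-to-face are counted in the wrong group.** No rebooking before the initial appointment is described. Defining groups by first allocation is a precaution.

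**Conclusion.** The point holds in a limited form. The assurance that selection bias is excluded is not supported, because it depends on a slot-division rule that the article does not give and on a process that was not randomised. The stated covariate list omits the allocation drivers that the article itself names. This is a possible bias in the between-pathway comparisons, not a demonstrated one.

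Its size ranges from about zero to several percentage points on a binary comparison. It is negligible if filling is unrelated to list position. It could approach the 8.5-point half-width only if imbalance and outcome difference are both large. These figures assume the urgent share, the filling rule and the outcome gap, and they are taken before adjustment. No corresponding figure was derived for appointment counts, time to treatment, costs or CO2eq.

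**What to change.** 1. Replace the guarantee in Recruitment with a statement that the booking process is intended to limit selection bias, and state how consecutive patients are divided between remote and face-to-face slots.
2. Add referral priority category and booking week (as stratum or fixed effect) to the regression models in Quantitative analysis and to the propensity model. List the propensity covariates and report balance by pathway before and after weighting.
3. Add waiting time at allocation only for outcomes of which it is not a component. It is part of referral-to-treatment time, so adjusting for it there would condition on part of the outcome. For that outcome, adjust for priority and for referral or booking week instead.
4. Define the comparison groups by the pathway first allocated in the booking system.

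The cost is modest: a few fields from the booking system (assuming it holds them), some extra model parameters, and changes of wording. Booking week and first allocation are easiest to capture prospectively, so this is best settled early. Allocation itself need not change.

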### Quantitative methodology

Quantitative methodology study process using questionnaires (figure 2):

Patients attending traditional pathway and new remote pathway recruited.Remote pathway participants: two questionnaires - first on the day of clinic attendance and second after completion of treatment or discharge.Traditional pathway participants: one questionnaire on the day of clinic attendance.

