## Methods and analysis

### Project setting

The study will be conducted across hospital and primary care outpatient clinics offered by UHB. Data will be collected from patients following all permutations of the remote pathway alongside standard ENT outpatient clinics, such as hospital outpatients, diagnostic hubs and primary care clinics. During appointments, patient data captured via the Endoscope-I software will be stored securely. Post-consultation, data will be transmitted through an encrypted cloud service and reviewed by ENT Consultants using secure, bespoke app-based software. Following completion of their outpatient pathway, consented patients will be asked to complete a follow-up questionnaire, and some will be invited to a semi-structured interview.

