### Secondary outcomes

Clinical throughput impact:Investigate impact of remote pathway on waiting times from referral to treatment.Compare the clinician time required per remote consultation to reach diagnosis/definitive treatment.Stakeholder acceptability:Examine barriers to implementation, training needs, scalability and throughput.Determine the optimal setting for data capture and assess geographic variation.Assess the impact across different demographics, especially under-served populations.Health economic analysis:Conduct a cost-consequences analysis detailing waiting times, quality of life, resource use, costs, time off work and productivity for both study groups.Perform cost-consequence and cost-utility analyses from an NHS perspective.Environmental sustainability:Calculate the direct (patient journey) and indirect (clinic output) carbon footprint of the ENT outpatient service by assessing carbon dioxide equivalents (CO_2_Eq) for both new and existing clinic models by location.

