This is an observational study, and we are not measuring the effect of an intervention. Our initial sample size calculations have been driven by similar pieces of implementation studies in the literature, looking into studies assessing non-inferiority interventions for remote/telehealth clinics, as well as assessing the potential financial benefit to the patients/service and the environmental impact,^11^,^15^ further informed by similar studies mapped through our team’s scoping review.^6^ Continuous sampling will be undertaken on both pathways until we reach a number of 150 participants from each group that have completed the initial questionnaires. The patients of the remote pathway will also be sent a follow-up questionnaire after their discharge, asking for their overall experience of the new service. The total of recruited participants will be expected to exceed the minimum of 300 we need for our analysis, and we will be allowing for a 10% attrition, as the current number for patients seen in face-to-face and remote clinics exceeds the 80 patients per cohort, per week. All the primary outcomes data will be extracted directly from the clinical notes of the patients, while the data of the secondary outcomes will be procured via questionnaires.

For the interviews, we will use a topic guide developed based on the existing literature and the research team’s experience of technology and innovation implementation, as well as service redesign.^16^,^18^ Through the interview process, we will investigate the experience of the different stakeholders involved in the remote pathway. We will undertake purposive sampling to select participants, expecting 30–35 participants in total, to allow for thematic saturation to take place.^19 20^ Participants in the interviews will be classified into two categories: patient participants and NHS staff. Recruitment will continue until overall thematic saturation has been achieved within each group. Patients enrolled will be approached, after completing the remote clinic pathway, while clinicians, managers and the other stakeholders will be given participation leaflets and invited via email or in person to participate in the study through interviews. If non-English speakers participate in the interviews, interpreters will also be facilitating the process.

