### Health economic methodology and analysis

A comprehensive health economic analysis will assess the cost-effectiveness of the remote model across settings. This will include an examination of NHS costs for training, equipment and service delivery (current tariffs), alongside economic benefits derived from improved patient outcomes and system efficiencies. Productivity will be assessed from both NHS and patients’ perspectives. Health utility will be assessed via PROMs and successful treatment/discharge from ENT care. Cost-consequence and cost-utility analyses will be undertaken in line with NICE guidelines.^24^ Data will be standardised and allocated to clinical pathways, with incremental cost-effectiveness ratios generated to compare models. Results will be summarised descriptively for each cost category, highlighting any pathways with a significant impact on overall costs or outcomes.

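### The post-treatment questionnaire goes to the remote group only, so the planned two-group comparison of quality of life and utility, and the cost-utility ratio built on it, has no comparator data

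*Protocol article*

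**What the plan says.** **Who is asked, and when.** Quantitative methodology gives remote participants "two questionnaires - first on the day of clinic attendance and second after completion of treatment or discharge". For the comparator it says: "Traditional pathway participants: one questionnaire on the day of clinic attendance". Recruitment agrees on the recipients and describes the content: "The patients of the remote pathway will also be sent a follow-up questionnaire after their discharge, asking for their overall experience of the new service".

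**Where the data come from.** Recruitment takes primary outcome data from clinical notes, "while the data of the secondary outcomes will be procured via questionnaires".

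**What is to be compared.** Secondary outcomes include: "Conduct a cost-consequences analysis detailing waiting times, quality of life, resource use, costs, time off work and productivity for both study groups". The same list adds a cost-utility analysis from the NHS perspective. Health economic methodology and analysis states: "Health utility will be assessed via PROMs and successful treatment/discharge from ENT care". It then plans incremental cost-effectiveness ratios between the two models.

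**What points the other way.** Project setting says: "Following completion of their outpatient pathway, consented patients will be asked to complete a follow-up questionnaire". That sentence is not restricted to the remote group. The Introduction defines the end of the study by the last questionnaire and interview follow-up of patient participants after treatment, again with no restriction by pathway.

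**The concern.** An incremental QALY needs a utility in each group after the pathways have had time to act. The schedule, given twice, collects a later questionnaire in one group only, while the outcomes and the economic section promise a two-group result.

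If the schedule is followed, two substitutes remain for the missing contrast, and neither answers the question:

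- A before-after change in the remote group alone mixes any pathway effect with natural recovery and regression to the mean.
- A comparison of remote follow-up values with traditional day-of-clinic values sets patients at different stages side by side.

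Cost-effectiveness against the face-to-face pathway is one of the study's stated aims. Post-treatment answers that were never requested from traditional patients cannot be properly recovered later.

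**Working it through.** **1. The plan's own figure.** Recruitment sets 150 per group (300 in total) completing the initial questionnaires, with a 10% attrition allowance. The article gives no significance level, power, effect size or SD, so 300 cannot be reproduced. This point does not depend on how it was derived.

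**2. Follow-up questionnaires available under Recruitment and Quantitative methodology.**

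| Group | Day of clinic | After treatment or discharge |
|---|---|---|
| Remote | 150 | up to 150; 150 × 0.9 = 135 with 10% attrition |
| Traditional | 150 | 0 |

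**3. Is the post-treatment difference estimable?** For a mean score, SE(difference) = SD × √(1/n_R + 1/n_T). With n_T = 0 the second term is undefined, so there is no estimate. The QALY has the same gap. With utility u0 on the clinic day and u1 at time t, the QALY is approximately t × (u0 + u1)/2. For traditional patients u1 is never observed, so the QALY difference, which is the denominator of the cost-utility ratio, is not identified.

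**4. Can the planned methods fill the gap?**

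- *Multiple imputation* (Quantitative analysis) would have no observed traditional follow-up value to learn from. Borrowing the remote group's values would assume that the pathways are equal, given the covariates, which is the question under study.
- *The Cox model* is planned for differing follow-up duration. It handles event times, not PROM scores that were never asked for.
- *Discharge as part of utility* could be read from notes in both groups. It is a process event that the pathway may itself change, and it is not a valuation of health.

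**5. Outcome by outcome, if the one-sided schedule is followed.**

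| Outcome | Two-group comparison |
|---|---|
| Post-treatment quality of life or utility, incremental QALY, cost-utility ratio | No comparator data |
| Productivity and time off work after the clinic day, from questionnaires | No comparator data |
| End-of-pathway experience | No comparator data |
| Experience on the clinic day | Estimable, but at different pathway stages |
| Productivity up to the clinic visit | Estimable, if asked on the day |
| Symptom resolution | No source stated; may come from notes |
| Primary outcomes, time to definitive treatment | Not affected; can come from notes |

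The difference in stage follows from Project setting: "Post-consultation, data will be transmitted through an encrypted cloud service and reviewed by ENT Consultants". On the clinic day a face-to-face patient attends a consultant-led clinic, while a remote patient's data have yet to be reviewed.

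**6. What a symmetric follow-up would give (illustration only).** With 135 per group, SE = √(2/135) = 0.122 SD and the 95% half-width is 1.96 × 0.122 = 0.24 SD. Assuming a two-sided 5% level and 80% power, the detectable difference is (1.96 + 0.84) × 0.122 = 0.34 SD; with 150 per group it is 0.32 SD. These figures are unadjusted, and propensity weighting would usually widen them. Keeping 150 per group at follow-up needs 150/0.9 = 167 per group, or 334 in total.

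**The case against.** The strongest reply is that the schedule is not settled. Project setting and the Introduction describe follow-up without limiting it to remote patients, and Figure 2, which shows the data capture points, is not available here. This stands to a degree: the count of 0 of 150 is conditional on Recruitment and Quantitative methodology. Those two sections are the specific ones, however, and they agree. At best the article contradicts itself on whether the comparator data will exist.

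A reader might infer that every comparison of secondary outcomes is lost. The documents do not support that:

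- The statement that secondary outcomes come from questionnaires cannot be exhaustive. Carbon footprint also uses clinic energy, consumables and government conversion factors, and costs use tariffs.
- Appointments to definitive treatment is a primary outcome taken from notes, so the notes must be followed that far. Referral-to-treatment time can therefore be taken from them in both groups.
- Symptom resolution appears only in Quantitative analysis and has no stated source.
- Both groups complete a day-of-clinic questionnaire. The difference in stage makes experience hard to interpret but does not make it inestimable.

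A reader might also infer that the traditional questionnaire precedes treatment. The article says only that it falls on the clinic day.

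Finally, the choice of PROM may be left to the full protocol, and its absence from the article is no fault. That does not rescue the schedule, because no analysis plan can analyse answers that were never collected. Recruitment describes the remote follow-up as asking about experience of the new service, so it is not clear that it carries a PROM even there.

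**Conclusion.** The point holds in a limited form. If Recruitment and Quantitative methodology are followed, none of the 150 traditional participants has a PROM after the clinic day. The two-group post-treatment difference in quality of life or utility, the incremental QALY and its ratio are then not identified, and post-clinic productivity from questionnaires and end-of-pathway experience lack a comparator. If the wording in the Introduction and Project setting governs instead, the comparison can be made, but the article must say so. The conclusion rests on taking the more specific schedule at its word; no assumption about effect size or SD enters it. It should be resolved before the comparative economic analysis is relied on, because the missing answers cannot be properly recovered afterwards.

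**What to change.** 1. Reconcile the Introduction and Project setting with Recruitment and Quantitative methodology on who receives the follow-up questionnaire.
2. Send both groups the same follow-up questionnaire, including the PROM used for utility and the productivity items. Use the same fixed time from referral or first appointment rather than discharge, whose timing the pathway may change. The sponsor should choose and justify the time point.
3. Put the utility PROM in the day-one questionnaire for both groups as well.
4. Ask the experience items that are meant for comparison once patients in both groups have had the consultant's decision, or state that day-of-clinic experience is measured at different stages.
5. Report discharge as a consequence in the cost-consequence analysis, not as a utility.

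If the sponsor keeps the one-sided follow-up, limit two-group claims to day-of-clinic and notes-based outcomes, and withdraw the comparative cost-utility analysis.

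The cost is an amendment, about 150 extra questionnaires to patients already consented, the effort of sending and chasing them, and some non-response in the traditional group.
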